### Study Measures and Data Collection

#### Overview

Study measures are presented by the study aim in Table 2, which includes the outcome, the instrument or data collection tool, a description of each assessment, and the schedule of assessments.

**Table 2. T2:** Measures, instruments, and assessment schedule.

Outcomes	Instruments or data collection tool	Description	Schedule
Feasibility and acceptability measures (aim 1)			
Screening	REDCap-generated reports	Number of patients screened for eligibility, proportion of screened patients who are eligible (eligibility rate), reasons for exclusion, and number of patients screened to identify one eligible participant.	Throughout the study
Recruitment	REDCap-generated reports	Number of participants invited to participate in the study. Number of participants who declined participation. Number of participants who signed the informed consent form. Percentage of eligible patients who consent (enrollment rate). Percentage of consented patients who complete baseline assessment and are randomized (randomization rate). The time required to achieve the target sample size (expressed in months). The number of participants enrolled per month (accrual rate).	Throughout the study
Retention	REDCap-generated reports	Proportion of participants who: complete the study (completion rate), voluntarily withdraw (withdrawal rate), and who are LTFU^a^ rate.	Throughout the study
Intervention fidelity	iCardia system report; and TAM^b^ [72] Survey (1-item self-report of messages read)	Percentage of TM^c^ successfully delivered. Participant postintervention self-report of overall TM read (none, some, about half, nearly all, or all).	Throughout the study
Assessment completion	REDCap-generated reports	Number of patients who completed 4-week and 12-week assessments.	Throughout the study
Acceptance and satisfaction	TAM^b^ [72] Survey (self-report)	23-item questionnaire assessing perceived usefulness, satisfaction, and acceptance of the TM intervention	12 weeks
Patient-reported outcomes (aim 2)			
Self-care	SCHFI^d^ v7.2 [13,73] (self-report)	Self-reported self-care assessed with 3 subscales: Self-Care Maintenance, Symptom Perception, and Self-Care Management. Subscale scores range from 0 to 100. A score of ≥70 indicates adequate HF^e^ self-care.	Baseline, 4 weeks, and 12 weeks

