#### Patient-Reported Health Outcome Measures (Aim 2)

The primary outcome of interest is HF self-care, assessed with the SCHFI version 7.2 [46] at baseline, 4 weeks, and 12 weeks. The SCHFI (29 items) has 3 subscales: Self-Care Maintenance (10 items), Symptom Perception (11 items), and Self-Care Management (8 items). Standardized scores in the SCHFI range from 0 to 100. A total score of 70 or more indicates adequate self-care [13,73].

Secondary patient-reported health outcomes include medication and refill adherence (ARMS), heart-healthy diet adherence (SDBHF), HF knowledge (Atlanta Heart Failure Knowledge Test [AHFKT]), health-related quality of life (Minnesota Living with Heart Failure Questionnaire [MLHFQ]), self-efficacy (Self-Care Self-Efficacy [SCSE]), and health beliefs (BDCS, BMCS, and BSMS) at baseline, 4 weeks, and 12 weeks.

As part of the safety protocol, the study team will review the EHR and record adverse events, serious adverse events, and unanticipated problems, including unplanned hospitalizations, emergency department visits, and mortality or death events for all enrolled participants.

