### Statistical Analysis Plan

#### Sample Size Justification for a Pilot RCT

Given the pilot nature of this RCT, the sample size was not based on a formal-efficacy-powered calculation. Instead, it was determined based on feasibility considerations and estimation of preliminary outcome variability. The main objectives of the study are to evaluate the feasibility, acceptability, and preliminary effects of the Text4HF intervention and to generate estimates of variability and effect sizes to inform a future, fully powered trial. The primary patient-reported outcome is HF self-care, measured using the SCHFI, which yields continuous scale scores and can be used to estimate between-group differences, variability, and effect sizes for a future definitive trial. Consistent with recommendations for pilot RCTs involving continuous behavioral outcomes [83,84], we determined that we need to enroll 30 participants and randomize them equally between study arms (n=15 per group) to inform a 90% powered trial with an expected standardized effect size in the medium range (0.3≤*d*<.7) [84]. This sample size is appropriate for estimating feasibility parameters, retention, intervention acceptability, and preliminary changes in SCHFI scores, while also providing estimates of SCHFI variability and effect size needed to design a future fully powered trial. Assuming up to 20% attrition over 12 weeks, approximately 24 participants are expected to complete the 12-week follow-up assessment. The target sample size also balances methodological recommendations for pilot RCTs with the available study resources, timeline, and anticipated recruitment capacity.

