#### Analysis Plan

The primary analyses comparing the intervention and usual care groups will follow the intention-to-treat principle, whereby participants are analyzed according to the group to which they were originally randomized, regardless of intervention adherence or exposure.

Standard descriptive statistics will be used to describe recruitment and retention rates, participant characteristics, and intervention acceptability. Chi-square tests and *t* tests will be used to examine differences between the groups in exploratory patient-reported outcomes (Table 2). Cohen *d* effect sizes will be used to evaluate the preliminary effect of the text messages on HF self-care measures as assessed by the SCHFI (Table 2). The significance level will be set at less than .05 for all analyses.

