## Discussion

### Anticipated Findings

Although TM has demonstrated effectiveness in self-management interventions, such as diabetes, hypertension, and obesity, evidence as a standalone study in individuals with HF is limited. Many of these studies on self-management are deployed in conjunction with remote patient monitoring. The Text4HF trial aims to address an important gap in the literature by providing preliminary evidence on the feasibility and efficacy of individually tailored text messages as a standalone intervention for improving self-care in middle-aged and older adult patients with HF. Given the potential for scalability, reach, and low cost of TM, this approach could evolve into a paradigm shift where TM could be deployed in an HF clinic. The study is not powered to establish efficacy; rather, it is intended to generate estimates of effect size and variability that will inform the design of a future fully powered RCT. We anticipate the study will demonstrate feasibility with recruitment and retention rates greater than 80%. Acceptability will be demonstrated with high rates of patient satisfaction and preliminary improvements in HF self-care compared with usual care.

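### A .05 significance level for all analyses does not fit a pilot sized for estimation: no observed effect inside the plan's expected range can be significant (two-sided), and the ones that are will be inflated

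*Protocol article*

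**What the plan says.** Under Analysis Plan, the protocol article compares the arms on the exploratory patient-reported outcomes with chi-square and t tests, and uses Cohen d for the preliminary effect on the SCHFI. It closes with: "The significance level will be set at less than .05 for all analyses". It mentions no confidence intervals and no adjustment for the number of tests, and does not say whether the tests are two-sided or at which visit they are run. Aim 1 (recruitment, retention, acceptability) is assigned descriptive statistics only.

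The Sample Size Justification says that the 30 participants do not come from an efficacy power calculation. They are meant "to inform a 90% powered trial", "with an expected standardized effect size in the medium range", given there as d from 0.3 to below 0.7. With up to 20% attrition, about 24 are expected to complete week 12. Under Anticipated Findings the article adds: "The study is not powered to establish efficacy".

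Table 2 lists three SCHFI subscales, medication adherence, diet adherence, quality of life, self-efficacy, heart failure knowledge and three health-belief scales, each at baseline, 4 weeks and 12 weeks.

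**The concern.** The stated purpose and the stated decision rule pull in different directions. An estimation pilot should deliver a between-group difference, a standard deviation and an honest statement of their uncertainty. A .05 rule instead sorts the outcomes into significant and not significant, in a sample where that sorting carries little information.

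Two consequences follow. First, an estimate that lands where the plan expects it would be labelled not significant. Second, an estimate that is significant has been selected for being large. If significant outcomes are the ones carried forward, the effect size handed to the next trial is too big and that trial too small. With 11 or more scores tested without adjustment, some of the significant ones may be chance alone. The Anticipated Findings section looks forward to preliminary improvement in self-care over usual care, so readers will probably look to these tests for a verdict.

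**Working it through.** **Inputs.** 30 randomized 1:1, 15 per arm; 20% attrition; expected d of 0.3 to below 0.7 (Sample Size Justification). Alpha .05 and t tests (Analysis Plan). 13 per arm randomized so far (Results). Scores and visits from Table 2. Assumed, because not stated: two-sided tests, equal arms, unadjusted comparison of final scores.

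**The plan's own figure.** 30 × (1 − 0.20) = 24 completers, about 12 per arm. This agrees with the article.

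**Smallest observed d with p<.05.** d_min = t(.975, 2n−2) × √(2/n).

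- n = 12: 2.074 × 0.408 = 0.85
- n = 13: 0.81
- n = 15: 2.048 × 0.365 = 0.75

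All three lie above 0.7. With one-sided tests the threshold would be 0.70 at 12 per arm and 0.62 at 15.

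**Power for a true d.** Noncentral t with noncentrality d × √(n/2) and 2n−2 degrees of freedom:

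| True d | 12 per arm | 13 per arm | 15 per arm |
|---|---|---|---|
| 0.3 | 10.8% | 11.4% | 12.5% |
| 0.5 | 21.6% | 23.2% | 26.2% |
| 0.7 | 37.5% | 40.3% | 45.7% |

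A true d of 1.20 at 12 per arm, or 1.06 at 15, would be needed for 80% power.

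**Inflation among significant results.** In a simulation with 12 per arm, the mean absolute d among significant results is about 1.08, 1.12 and 1.17 for a true d of 0.3, 0.5 and 0.7. As an illustration, required sample size goes with 1/d². Planning on 1.12 when the truth is 0.5 would make the next trial too small by a factor of (1.12/0.5)² ≈ 5.

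**Number of tests.** 3 SCHFI subscales + 5 (medication adherence, diet adherence, quality of life, self-efficacy, knowledge) + 3 belief scales = 11 scores. This is 11 tests if only week 12 is tested, and 11 × 2 = 22 if both follow-up visits are.

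| Tests | Expected false positives, global null | At least one, if independent |
|---|---|---|
| 11 | 11 × .05 = 0.55 | 1 − 0.95^11 = 43% |
| 22 | 22 × .05 = 1.1 | 1 − 0.95^22 = 68% |

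For 22 equally correlated tests, simulation puts the chance of at least one at about 57%, 44% and 30% for correlations of 0.3, 0.5 and 0.7.

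**The case against.** The article is open about its limits. It says that the study is not powered for efficacy, calls the tested outcomes exploratory, already plans Cohen d for the SCHFI, and asks under Limitations for cautious reading. Nothing in it ties progression to the next trial, or any efficacy claim, to p<.05. The d range is given for the future trial, so a pilot that cannot reliably detect it breaks no promise. All of this stands and lowers the severity. It does not remove the .05 rule, which is stated for all analyses without an exception for Aim 2. The caution under Limitations rests on self-report and lack of blinding, not on power or the number of tests.

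Three stronger readings are tempting, and the documents do not support them:

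- A reader might infer that the trial cannot detect any effect in the expected range, or that a true effect of the expected size is bound to be reported as not significant. That confuses true with observed d. The thresholds of 0.75 and 0.85 apply to the estimate; a true d near 0.7 still has 38% to 46% power.
- A reader might infer that the p values can only mislead. Given the article's own caveats, the risk is real but limited.
- A reader might take 22 tests and a 68% error chance as facts. The article does not say which visits are tested, and overlapping self-report scales in the same patients are unlikely to be independent.

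The choice of a lead subscale and visit may be made in a statistical analysis plan that is not shown, so its absence here is not held against the article.

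**Conclusion.** The point holds as a mismatch between the significance rule and the pilot's declared purpose. Power is 11% to 38% at 12 per arm, and 13% to 46% at 15, over the range expected for the future trial. No observed d within that range reaches two-sided p<.05 at 12, 13 or 15 per arm. A significant SCHFI result would therefore overstate any true effect in that range, which is the quantity the pilot exists to supply. The unadjusted tests number 11 or 22, depending on the visits used.

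The figures rest on two-sided, unadjusted t tests with equal arms. One-sided testing would raise power at 12 per arm to between 18% and 51%, and at 15 per arm would bring the threshold inside the range. Baseline adjustment would also raise power. The article states neither. Because the outcomes are labelled exploratory and no decision hangs on p<.05, this is a should-fix item and does not threaten the trial.

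**What to change.** For Aim 2, replace the .05 sentence with: *Between-group differences and Cohen d are reported with 95% confidence intervals; any p values are descriptive, no significance threshold is applied and no efficacy claim is made.*

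The intervals will show plainly what the pilot can say. With 12 per arm, an observed d of 0.5 has an approximate 95% interval of −0.31 to 1.31, from 0.5 ± 1.96 × √(2/n + d²/(4n)).

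The change needs no new data and no extra participants, and can be made before the analysis. The cost is giving up a statement of significance.

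As a separate minor point, reconcile the SCHFI scoring. The section on patient-reported outcome measures says "A total score of 70 or more indicates adequate self-care", whereas Table 2 says "Subscale scores range from 0 to 100" and attaches the cut of 70 to the subscale description. The text should say which score the cut applies to.

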### Data Collection and Management Procedures

This study uses three systems for data collection and intervention delivery: (1) REDCap, (2) Epic, and (3) iCardia. The REDCap database is used for documenting screening, enrollment, and storing intervention-related data. The Epic UI Health electronic health records system is used to abstract clinical data and document informed consent from enrolled participants. iCardia [71] is a secure, internet-based application that was developed at the university and is used to program and send TM. All data are verified, cleaned, and analyzed using SPSS (version 30.0; IBM Corp).

### Ethical Considerations

The study is conducted in accordance with the Declaration of Helsinki, the International Council for Harmonization (Good Clinical Practice), and the laws and local regulations applicable in the United States. The study is approved by the Institutional Review Board (IRB protocol #2022‐0704) and is registered at ClinicalTrials.gov. Appropriate IRB waivers for electronic medical record review and research participant recruitment were granted by the University of Illinois Chicago IRB. Trained research assistants obtain informed consent using the REDCap [47] eConsent Framework once eligibility and patient interest are confirmed. Trained research assistants obtain informed consent via the REDCap [47] electronic consenting platform once eligibility and patient interest are confirmed. As part of our safety monitoring protocol, we record all hospital admissions, emergency room visits, and deaths. These events are documented in the study record by a study team member. Participants receive US $30 per study visit as compensation for their time and effort for a total of US $60 if both assessments are completed.

To protect the privacy of study participants and to maintain the confidentiality of the data, all datasets created in this study are stored electronically in secure, password-protected, and encrypted databases. All human participants are assigned a Subject ID code in REDCap, which is used during data collection throughout the study. All computerized and database systems used in this study for data collection and analysis are password-protected and encrypted, and will be accessible only to the University of Illinois Chicago key research personnel.

### Dissemination Plan

The findings from this trial will be disseminated at a conference as a poster or oral presentation, as well as through a manuscript that will be published in an open access, peer-reviewed journal.

## Results

This trial is funded by the Midwest Roybal Center for Health Promotion and Translation in June 2022 and received approval from the University of Illinois Chicago IRB. Start-up activities were completed by August 2024, including obtaining IRB approval, creating data collection instruments, developing the TM library, and testing the TM algorithm. Recruitment began in September 2024. Overall, 26 participants have enrolled in the study and have been randomized to the intervention group (n=13) and the control group (n=13). The mean age of participants is 60 (SD 6.62) years, and 46% (12/26) are female. Regarding self-identified race, 73% (19/26) are non-Hispanic Black. The majority of the patients are clinically evaluated as NYHA Class II (19/26, 73%), with 50% (13/26) diagnosed with reduced ejection fraction. The estimated completion date of the study is June 30, 2026. Results of the study are expected to be published later this year or in 2027.

## Discussion

### Anticipated Findings

Although TM has demonstrated effectiveness in self-management interventions, such as diabetes, hypertension, and obesity, evidence as a standalone study in individuals with HF is limited. Many of these studies on self-management are deployed in conjunction with remote patient monitoring. The Text4HF trial aims to address an important gap in the literature by providing preliminary evidence on the feasibility and efficacy of individually tailored text messages as a standalone intervention for improving self-care in middle-aged and older adult patients with HF. Given the potential for scalability, reach, and low cost of TM, this approach could evolve into a paradigm shift where TM could be deployed in an HF clinic. The study is not powered to establish efficacy; rather, it is intended to generate estimates of effect size and variability that will inform the design of a future fully powered RCT. We anticipate the study will demonstrate feasibility with recruitment and retention rates greater than 80%. Acceptability will be demonstrated with high rates of patient satisfaction and preliminary improvements in HF self-care compared with usual care.

### Comparison With Prior Work

In 2019, Chen et al [85] conducted a large (n=767) RCT in China that provided one-way, Heart Failure Society of America-based, educational TMs for a month to patients recently discharged from a HF-related hospitalization [40]. While the Chen et al [85] study illustrated that this approach is feasible and cost-saving, the messages were not individually tailored. iCardia4HF [42] was a complex, multicomponent mHealth intervention that included several Bluetooth-enabled devices and mobile apps, along with individually tailored TMs. The TMs created in iCardia4HF were based on the Heart Messages program [43] and focused on 3 critical domains: adherence to loop diuretics, a low-sodium diet, and self-monitoring of weight and edema. However, there is a need to further enhance and expand the existing messages. The messages should holistically address unhealthy lifestyle behaviors and ensure that the program aligns with the latest clinical guidelines for patients with HF. Additionally, it is equally important to assess the independent effect of individually tailored TMs to improve HF self-care as a standalone intervention.

Cornelius et al [86] targeted patients with HF in a small (n=30) randomized controlled pilot study involving urban patients who were provided with 2-way TM reminders to improve depression and anxiety [87]. However, TMs were used to deliver questions for the reinforcement of cognitive behavioral therapy sessions and did not include self-care related content.

The MESSAGE-HF was a large (n=699) RCT involving TM in conjunction with nurse-led telemonitoring [88]. The dose (frequency) of messages was adjusted based on the telemonitoring feedback. However, the authors reported no clinically meaningful changes in clinical laboratory levels, mortality, or hospitalizations [88].

### Strengths

TM is widely used and has the potential to meet the needs of patients with varying levels of technology literacy. Prior studies of TM interventions have used a one-size-fits-all approach where all patients receive a fixed dose of messages regardless of their health beliefs, knowledge of their condition, or experience with self-care. Personalization or tailoring of the messages is usually centered on including participants’ names or using other surface-level approaches. Only one other study, iCardia4HF, has used this methodology to improve self-care behavior, but it combined TM with multiple mHealth apps and connected health devices, making it difficult to assess the effects of TM as a standalone intervention [59].

The patient population demographics in the Text4HF study are approximately 80% Black or African American, 10% Hispanic or Latinx, and 10% White. This study will provide valuable data on addressing gaps in research with respect to enrolling older, low-income Black or African American patients with HF who carry the highest risk of hospitalization, morbidity, and mortality [17]. Additionally, women have traditionally been underrepresented in HF research [89-92], and this study is well-positioned to address these gaps.

The Text4HF study has the potential to address the needs of patients with HF through a simple, low-technological, yet sophisticated intervention. Improvements in patient HF self-care among patients using existing technology represent an exciting way to reach patients in the community with a low-cost solution.

### Limitations

This study has a few limitations. First, this is a single-site pilot study recruiting participants from an urban academic hospital setting. The population consists predominantly of patients from racial and ethnic minority groups and may not be generalizable to other demographic populations. Second, perceptions may play a role in the results because they are based on patient-reported outcomes (self-care), and the lack of blinding may contribute to performance bias. Therefore, since this is a stage I behavior change intervention, the results on the preliminary effect of the intervention on exploratory patient-reported outcomes from this study should be interpreted cautiously.

### Future Directions

The Text4HF intervention will provide data on feasibility, acceptability, and preliminary efficacy to refine the study for a larger clinical trial in the future. Future work involving TM in HF may provide the basis for deploying this methodology into clinical practice.
